### 2.3 Randomization, assignment, and blinding

Participants are stratified according to the grade of ARII at admission, and then randomly assigned to routine treatment alone and in combination with local glucocorticoids groups at a ratio of 1:1 within each stratum. The randomization sequence will be generated by computer system. The trial-group assignments are open-label to the participants and physicians.

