### 2.5 Study endpoints

The primary endpoints include the recovery and improvement of ARII after treatment. The secondary endpoints include the recurrence and aggravation of ARII, and adverse events during hospitalization and follow-up periods.

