The grade of intestinal mucosal damage on colonoscopy is evaluated in accordance with the Vienna rectal score (Wachter et al., 2000), as follows.(1) Grade 0 is defined as only localized mucosal hyperemia and edema.(2) Grade 1 is defined as diffuse non-confluent mucosal hyperemia and edema with single telangiectasia but without ulcer, stenosis, and necrosis.(3) Grade 2 is defined as diffuse and confluent mucosal hyperemia and edema with multiple non-confluent telangiectasia but without ulcer, stenosis, and necrosis.(4) Grade 3 is defined as unlimited mucosal hyperemia and edema with multiple and confluent telangiectasia, and the area of superficial ulcer is less than 1 cm^2^, but without stenosis and necrosis.(5) Grade 4 is defined as unlimited mucosal hyperemia, edema, and telangiectasia, and the area of superficial ulcer is more than 1 cm^2^, and the diameter of lumen diameter is more than 2/3 of the regular lumen diameter, but without necrosis.(6) Grade 5 is defined as unlimited mucosal hyperemia, edema, and telangiectasia with deep ulcer, fistula, or perforation, and the diameter of lumen diameter is less than 1/3 of the regular lumen diameter, and presence of necrosis.

Recovery is defined as patients’ clinical symptoms and intestinal mucosal damage on colonoscopy disappear. Improvement is defined as patients’ clinical symptoms alleviate or the Vienna rectal score decreases at least one grade.

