### 2.8 Data collection

The following data will be collected: (1) demographic data (i.e., gender and age); (2) history of malignancy; (3) interval between radiotherapy and occurrence of ARII; (4) history and type of medications for ARII before admission; (5) height, weight, and vital signs (i.e., body temperature, heart rate, blood pressure, and respiratory rate); (6) clinical symptoms (i.e., abdominal pain, distension, diarrhea, frequency of defecation, tenesmus, hematochezia, mucous stool, nausea, vomiting, acid reflux, and heartburn); (7) laboratory data (i.e., red blood cells, hemoglobin, white blood cells, neutrophils, lymphocytes, procalcitonin, c-reactive protein, IL-6, IL-2, TNF-α, IFN-γ, potassium, sodium, calcium, iron, and stool routine test); (8) grade of intestinal mucosal damage on colonoscopy; (9) histology of colorectal mucosa; and (10) intestinal obstruction, fistula, perforation, and/or stricture.

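### The symptom route to the primary endpoint "improvement" has no scale or minimum change, is enough on its own, and is rated open-label

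*Protocol article*

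**What the plan says.** Section 2.5 of the protocol article names two primary endpoints: "The primary endpoints include the recovery and improvement of ARII after treatment". It gives no visit beyond that.

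Section 2.7 defines both. On the first it says: "Recovery is defined as patients’ clinical symptoms and intestinal mucosal damage on colonoscopy disappear". The second asks for less, and a patient meets it when "clinical symptoms alleviate or the Vienna rectal score decreases at least one grade". Recovery joins its two parts with "and"; improvement joins its two parts with "or".

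The same section sets out a clinical scale, RTOG/EORTG grade 0 to IV. Sections 2.2 and 2.3 use that grade for eligibility and stratification. The definition of improvement does not use it.

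On masking, section 2.3 says: "The trial-group assignments are open-label to the participants and physicians". No blinded assessor is mentioned. Patients are "randomly assigned to routine treatment alone and in combination with local glucocorticoids groups at a ratio of 1:1 within each stratum", and section 2.4 describes no sham or saline enema for the control arm.

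Section 2.6 sizes the trial on improvement: 97.7% with and 72.1% without glucocorticoids, two-sided alpha 0.05 (sidedness from section 2.15), 80% power, 10% dropout, 30 per group. Section 2.12 and Table 1 schedule repeat colonoscopy only at months 3 and 12, while clinical symptoms are collected on day 7 and at months 1, 3, 6 and 12.

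**The concern.** The two routes to improvement are not equally well fixed. The Vienna route needs a fall of at least one grade on a six-level score. The symptom route needs only that symptoms have eased. The definition does not say on what scale, by how much, in which symptoms, or what happens when one symptom eases and another worsens. Because of the "or", an unchanged colonoscopy cannot overrule a lenient symptom rating. On day 7 and at month 1 no colonoscopy is scheduled, so improvement at those visits can rest only on the symptom route.

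Patients who know they received a week of active enemas, and physicians who know they prescribed them, may be readier to report or record that symptoms have eased. A criterion without a threshold offers little resistance to that. At stake is the endpoint that sets the sample size: a significant difference could partly reflect how symptoms were rated.

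**Working it through.** **1. The plan's own figure.** Inputs from section 2.6: p1 = 0.977, p2 = 0.721, 80% power, 10% dropout; two-sided alpha 0.05. With unpooled variance:

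n = (1.960 + 0.842)² × [p1(1 − p1) + p2(1 − p2)] / (p1 − p2)²
= 7.85 × (0.0225 + 0.2012) / 0.0655 = 26.8, so 27 per group.

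27 / (1 − 0.10) = 30 per group. The stated figure reproduces, which confirms that improvement alone drives the sample size.

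**2. What the rule requires.**

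| Part of the definition | Scale | Minimum change | Sufficient alone? |
|---|---|---|---|
| Vienna route of improvement | Vienna rectal score, 0 to 5 | One grade | Yes |
| Symptom route of improvement | None stated | None stated | Yes |
| Recovery | Symptoms and mucosal damage | Both disappear | Neither part is |

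**3. Illustration of what open-label rating could do.** The assumptions are mine, not the document's: no true effect, 72.1% truly improved in both arms, 30 analysed per arm, and some truly non-improved enema patients rated as improved. Under that null, 1 − 0.721 = 27.9% of the enema arm is non-improved, or 0.279 × 30 = 8.4 patients. A shift of s in the whole arm means misrating s / 0.279 of those patients.

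For each s, the probability of P < 0.05 favouring glucocorticoids is the sum, over all pairs (a, b) that are significant with a > b, of Bin(a; 30, 0.721 + s) × Bin(b; 30, 0.721). Chi-square is uncorrected. Section 2.15 names both tests.

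| Shift in whole arm | Share of non-improved misrated | Chi-square | Fisher's exact |
|---|---|---|---|
| 0 | 0 | 2.5% | 1.3% |
| 5 points | 18% | 6.3% | 3.6% |
| 10 points | 36% | 14.5% | 9.0% |
| 15 points | 54% | 29.8% | 20.0% |
| 20 points | 72% | 54.4% | 39.5% |

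On the other scale, misrating 10%, 20% or 30% of non-improved enema patients gives 4.2%, 7.0% or 11.2% by chi-square.

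Ten points is 0.10 × 30 = 3 patients, but those are 3 of about 8.4 non-improved patients. Both scales are needed to judge how plausible a shift is.

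**The case against.** The strongest reply is that the bias is inferred. The document reports no shift in rating, and a lenient criterion also lifts the control arm, whose routine treatment includes antidiarrheals, antibiotics and argon plasma coagulation. Both arms could then drift towards a ceiling and a real difference could be diluted. This stands as a limit: the direction is plausible because assignment is known and only one arm has an enema, but the document does not show that rating would shift in one arm only. Recovery, the other primary endpoint, is also stricter, though it does not size the trial.

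Three stronger readings are tempting and are not supported.

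- A reader might infer that easing of any one of the collected symptoms makes a success. Section 2.8 does list "abdominal pain, distension, diarrhea, frequency of defecation, tenesmus, hematochezia, mucous stool, nausea, vomiting, acid reflux, and heartburn", 11 items in all. But that is a data-collection list, and section 2.7 does not tie the endpoint to it. The Introduction describes the condition by abdominal pain, diarrhea and tenesmus, and no grade criterion mentions nausea, vomiting, reflux or heartburn. What holds is that the definition does not say which symptoms count.
- A reader might infer that the Discussion contradicts this definition, since it faults the source trial's assessment as subjective and poorly described. That criticism concerns mucosal repair only, and the Vienna score with its one-grade fall answers it.
- A reader might infer that slight leniency would produce a false positive. The larger error rates above need 36%, 54% or 72% of non-improved enema patients to be misrated, which is not slight.

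Finally, a full protocol may hold symptom-scoring rules that a condensed article omits. That would excuse a missing detail. Here the article states the rule for a primary endpoint, and the rule as stated has no threshold.

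**Conclusion.** The point holds. As written, the symptom route of improvement has no scale, minimum change or choice of symptoms, is sufficient alone, and is rated with assignment known. The endpoint that sizes the trial is thus open to assessment bias, plausibly in favour of the enema arm.

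Its size cannot be taken from the document. The 10-point case (14.5% by chi-square, 9.0% by Fisher's exact test) rests on an assumed shift, a true null at the section 2.6 control rate and 30 analysed per arm. It shows what the rule would allow and does not forecast what will happen. The change should be made; the trial's design can otherwise stay as it is.

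**What to change.** In section 2.7, define clinical improvement as a fall of at least one RTOG/EORTG grade from the grade at randomisation, and clinical recovery as grade 0. Record the grade at one named primary visit at which symptoms are already collected. State whether a Vienna fall remains an alternative route to improvement; if it does, the choice of visit must allow for colonoscopy only at months 3 and 12. Treat symptoms outside the grade criteria as descriptive.

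The cost is protocol wording and one case report form field, with no extra assessor. There are three drawbacks. Success rates may fall in both arms, so the 97.7% and 72.1% in section 2.6, and the sample size that follows from them, need rechecking. Grades II and III turn partly on treatment given by physicians who know the assignment, so some unblinded judgement remains and the bias is reduced, not removed. And no threshold can separate an effect of dexamethasone from an effect of the enema itself, because the control arm has none.

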### 2.8 Data collection

The following data will be collected: (1) demographic data (i.e., gender and age); (2) history of malignancy; (3) interval between radiotherapy and occurrence of ARII; (4) history and type of medications for ARII before admission; (5) height, weight, and vital signs (i.e., body temperature, heart rate, blood pressure, and respiratory rate); (6) clinical symptoms (i.e., abdominal pain, distension, diarrhea, frequency of defecation, tenesmus, hematochezia, mucous stool, nausea, vomiting, acid reflux, and heartburn); (7) laboratory data (i.e., red blood cells, hemoglobin, white blood cells, neutrophils, lymphocytes, procalcitonin, c-reactive protein, IL-6, IL-2, TNF-α, IFN-γ, potassium, sodium, calcium, iron, and stool routine test); (8) grade of intestinal mucosal damage on colonoscopy; (9) histology of colorectal mucosa; and (10) intestinal obstruction, fistula, perforation, and/or stricture.

### 2.9 Follow-up

All participants will be followed on the 1st, 3rd, 6th, and 12th month after treatment. Clinical symptoms, physical examinations, and laboratory tests will be collected. Adverse events will be monitored. Survival status will be recorded, including the major cause and date of death.

### 2.10 Treatment termination

Causes of treatment termination include: (1) participants request to terminate their assigned treatment; (2) participants’ conditions worsen and are not appropriate to continue their assigned treatments; (3) participants’ adherence is poor; (4) adverse events occur; and (5) pregnancy. In this setting, the assigned treatment will be discontinued, but the follow-up observation of these participants is still conducted.

### 2.11 Withdrawal

Participants can withdraw from the trial at any time due to the following reasons: (1) participants withdraw their informed consents; (2) study termination or center closure; (3) loss to follow up; and (4) death.

### 2.12 Study schedule

The study treatment and assessment plan are summarized in Table 1.(1) Eligible participants will be enrolled after signing their informed consents.(2) Demographic data, medical history, clinical symptoms, physical examinations, laboratory tests, abdominal computed tomography (CT) images, and description under colonoscopy will be collected before treatment.(3) Repeated abdominal CT scans will be performed on the 6th month after treatment.(4) Repeated colonoscopy will be performed on the 3rd month and 12th month after treatment.(5) Adverse events and survival status will be collected on the 7th day, 1st month, 3rd month, 6th month, and 12th month after treatment.

**TABLE 1 T1:** Study schedule.

Procedure	Screening	Treatment period 7th day	Follow-up period			
			1st month	3rd month	6th month	12th month
Informed consent	√					
Eligibility criteria	√					
Demographic data	√					
Medical history	√					
Clinical symptoms	√	√	√	√	√	√
Physical examinations	√	√	√	√	√	√
Laboratory tests	√	√	√	√	√	√
Abdominal computed tomography	√				√	
Colonoscopy	√			√		√
Adverse events		√	√	√	√	√

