## 2 Methods

### 2.1 Study design

In this multicenter RCT, patients with grade II-III ARII will be screened. The investigators from each center will sufficiently explain the objectives and harms of this study to potentially eligible participants. Once the participants agree and sign written informed consents, they will be randomly assigned at a ratio of 1:1 to routine treatment alone and in combination with local glucocorticoids groups. The data will be collected at admission, after treatment, and during follow-up periods (Figure 1). This study follows the Declaration of Helsinki, and the ethical approval number from medical ethical committee of the General Hospital of Northern Theater Command is Y (2024) 052-1. It has been registered in the *ClinicalTrials.gov.* Website (registration number: NCT06410443).

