### 2.4 Treatment

Routine treatment includes antibiotics, probiotics, vitamins, antidiarrheal drugs, enteral nutrition, and endoscopic argon plasma coagulation according to the current practice guideline (Wang and Wang, 2018). These drugs and procedures are selected based on the patients’ disease conditions and their availability at each site.

Local glucocorticoids refer to retention enema of dexamethasone 10 mg combined with 100 mL of 0.9% sodium chloride injection once daily for a duration of 7 days. It requires the solution to be retained in the bowel for more than 1 h.

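### Recovery, a primary endpoint set after treatment with no visit named, needs a colonoscopy that is not repeated until month 3

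*Protocol article*

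**What the plan says.** On timing, Section 2.5 states: "The primary endpoints include the recovery and improvement of ARII after treatment". No day or month is attached. Section 2.1 treats this phase as distinct from later visits: "The data will be collected at admission, after treatment, and during follow-up periods". The enema course in Section 2.4 is given "once daily for a duration of 7 days", and the only post-baseline column of Table 1 outside follow-up is the 7th day of the treatment period.

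On definition, Section 2.7 states: "Recovery is defined as patients’ clinical symptoms and intestinal mucosal damage on colonoscopy disappear". For the other endpoint it states: "Improvement is defined as patients’ clinical symptoms alleviate or the Vienna rectal score decreases at least one grade". Recovery joins symptoms and endoscopy with *and*; improvement joins them with *or*.

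On schedule, Section 2.12 states: "Repeated colonoscopy will be performed on the 3rd month and 12th month after treatment". Table 1 agrees: colonoscopy is ticked at screening, month 3 and month 12 only, while symptoms are recorded at every visit.

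On size, Section 2.6 powers the trial on improvement alone (97.7% against 72.1%, alpha 0.05, power 80%, dropout 10%) and arrives at 30 per group.

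**The concern.** The protocol states an endpoint time, an endpoint definition and an examination schedule that do not fit together. If the primary endpoints are read when the 7-day course ends, nobody can be classed as recovered, because the required examination is not done then. Improvement loses its endoscopic limb and rests on reported symptoms in a trial where participants and physicians know the allocation (Section 2.3).

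If the endpoints are read later, the protocol does not say when. Improvement could be read at five visits and recovery at two. A choice of visit made after outcomes are known would make the primary result depend on the data. Testing at several visits without adjustment would raise the false-positive rate above 5%.

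**Working it through.** **1. Visits against definitions** (Table 1 and Section 2.7)

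| Visit | Symptoms | Colonoscopy | Recovery | Improvement |
|---|---|---|---|---|
| Day 7 | yes | no | cannot be confirmed | symptoms only |
| Month 1 | yes | no | cannot be confirmed | symptoms only |
| Month 3 | yes | yes | scorable | symptoms or Vienna score |
| Month 6 | yes | no | cannot be confirmed | symptoms only |
| Month 12 | yes | yes | scorable | symptoms or Vienna score |

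At three of five post-baseline visits a patient with persisting symptoms can be called not recovered, but no patient can be called recovered.

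**2. The plan's own sample size.** Section 2.6 does not say which variance formula was used. The unpooled two-sided formula reproduces its figure:

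n = (1.960 + 0.842)² × [0.977 × 0.023 + 0.721 × 0.279] / (0.977 − 0.721)² = 7.849 × 0.2236 / 0.0655 = 26.8, so 27 evaluable per arm; 27 / 0.90 = 30.

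Power at 27 per arm = Φ(0.256 / √(0.2236/27) − 1.960) = Φ(0.853) = 80.3%. This refers to improvement at one unspecified time. No power is stated for recovery.

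**3. One fixed visit.** Each endpoint is tested once, so timing adds no inflation. Power for improvement stays near 80% if the planning rates hold at that visit.

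**4. Visit left open, each visit tested at 0.05.** This analysis is assumed; the protocol does not state it. With independent visits the chance of at least one false positive is 1 − 0.95^k: 9.75% for k = 2 and 22.6% for k = 5. For correlated visits, 20,000 trials were simulated with 27 per arm, a rate of 72.1% in both arms at every visit and equicorrelated latent normals. The test was chi-square, or Fisher's where an expected count fell below 5.

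| Correlation | Two visits | Five visits |
|---|---|---|
| 0.5 | 10% | 22% |
| 0.7 | 10% | 20% |
| 0.9 | 9% | 16% |

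A single visit rejects in 5–6%. Using chi-square throughout gives 9.4–10.2% for two visits and 15.8–23.2% for five at the same correlations.

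**5. Same visits with a Bonferroni correction.** Replacing 1.960 by 2.241 (0.05/2) or 2.576 (0.05/5) gives power Φ(2.813 − 2.241) = 72% or Φ(2.813 − 2.576) = 59%. Restoring 80% would need 37 or 45 per group after dropout.

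**6. If the control rate is higher than planned.** This could follow from counting improvement at any visit, or from spontaneous healing by month 3. The documents give no such rates, so a range is shown, using the formula of step 2 at 27 per arm.

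| Control rate | Power, glucocorticoid rate 97.7% | Power, glucocorticoid rate 99.9% |
|---|---|---|
| 75% | 73% | 85% |
| 80% | 58% | 73% |
| 85% | 40% | 58% |
| 90% | 22% | 40% |

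These are normal-approximation figures near the ceiling. Section 2.15 names chi-square and Fisher's tests, whose exact power at the planning rates and 27 per arm is 85% and 63%. The table shows direction and rough size only.

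**The case against.** The phase wording is not airtight. Section 2.9 says "All participants will be followed on the 1st, 3rd, 6th, and 12th month after treatment", and Section 2.12 uses the same words for months 3 and 12. On that usage the colonoscopy visits also fall after treatment and recovery can be scored at them. The mention of hospitalization and follow-up in Section 2.5 may attach to adverse events alone, so it does not settle the matter. This stands: the text is ambiguous and does not prove that day 7 was meant. It does not remove the need to name a visit, because on either usage the protocol leaves the time of a primary endpoint unstated.

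The powered endpoint also survives the day-7 reading. Improvement can be met on symptoms alone, and Section 2.6 makes no claim for recovery. This stands too.

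A reader might infer that every reading of the plan fails, or that leaving the visit open removes the stated power. The documents support neither. A single fixed colonoscopy visit is a third reading that works. No section says that improvement is tested at each visit or counted if present at any visit, and the handling of repeated assessments may lie in a document not shown. Inflation and power loss also belong to different hypothetical analyses: one test of improvement at any visit carries no inflation. Its power depends on rates the documents do not give, and they do not say whether 97.7% and 72.1% are single-visit or cumulative.

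**Conclusion.** The point holds as a conflict between stated sections. Sections 2.1, 2.5, 2.7 and 2.12 do not yield a time at which both primary endpoints are defined, and recovery cannot be confirmed at day 7, month 1 or month 6. Improvement at those visits is a symptom-only outcome under open-label conditions. This follows from the text and Table 1 without any assumption.

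The numerical consequence is conditional. If visits are tested separately and unadjusted, the false-positive rate is about 9–10% over two visits and 16–22% over five. That rests on 27 evaluable per arm, equal rates of 72.1% at every visit and correlations of 0.5–0.9. Counting improvement at any visit could lower power, by an amount the documents do not fix. The sample size of 30 per group reproduces and is not itself shown to be wrong.

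**What to change.** Reconcile Sections 2.1, 2.5, 2.7 and 2.12 by naming in Section 2.5 one assessment visit for each primary endpoint, compared with the screening value and tested once.

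- **Recovery:** a visit with colonoscopy. Month 3 is the first one scheduled.
- **Improvement:** month 3 as well, if the Vienna limb is to count; otherwise state that it is a symptom-only endpoint at day 7.
- **Other visits:** secondary, not further chances to meet a primary endpoint.
- **Sample size:** add to Section 2.6 that the planning rates are assumed to hold at the chosen visit.

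Make the change before any outcome data are examined. It is a wording change and adds no visit or procedure. The cost is statistical: by month 3 spontaneous healing may lift the control rate above 72.1% and narrow the difference. With 97.7% on glucocorticoids, a control rate of 80% would leave about 58% power on the formula that reproduces the plan's figure. If that is thought likely, the sample size should be revisited with the choice of visit.
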